## **4 EFFICACY ENDPOINTS**

### **4.1 Primary Efficacy Endpoint**

The primary endpoint will be the change in rate pressure product (heart rate x systolic blood pressure) from baseline (pre-exposure) to the end of a 3-hour simulated heatwave exposure.

## 4.2 Tertiary Efficacy Endpoints

The tertiary endpoints will be the change from baseline to the end of a 3-hour simulated heatwave exposure in: core temperature, whole-body sweat rate (whole-body sweat loss/duration of heat exposure), thermal comfort and thermal sensation.

## 5 STATISTICAL METHODOLOGY

### 5.1 Statistical Considerations

Statistical analyses will be performed using SAS Version 9.4 or higher. Unless otherwise specified, all statistical tests will be two-sided and performed at a significance level of 0.05.

Prior to all parametric analyses, basic assumptions will be checked and if they are violated, non parametric analyses will be performed to confirm results from the parametric analyses. If outliers are identified, analysis with and without the outliers may be presented.

In the event that a participant did not complete the 180 minutes heatwave exposure, the change from baseline will be calculated using the last measure available.

### 5.2 Efficacy Analysis

All efficacy analysis will be conducted on the Full Analysis set.

#### 5.2.1 Primary Analysis

The following descriptive statistics will be presented for the primary endpoint (change from baseline in rate pressure product) under the 38°C and 60% RH heatwave exposure: mean, standard deviation, median, Q1, Q3, minimum and maximum.

A restricted maximum likelihood (REML)-based linear mixed model including a term for condition and accounting for repeated measures, will be used to compare the change from baseline in rate pressure product under the 38°C and 60% RH heatwave exposure under the following conditions: control, fan alone, skin wetting alone and fan + skin wetting. Contrasts under this model will allow for the three main comparisons:

- Control vs. fan alone
- Control vs. skin wetting alone
- Control vs. fan + skin wetting

Differences between the control condition and each of the 3 other conditions will be tested and presented with point estimate along with 98.33% confidence intervals. These three comparisons will be tested at the 0.0167 significance level to control for the multiplicity of tests.

The assumption of normality underlying this model will be checked.

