#### 4.6 *Data collection protocol:*

The preliminary sessions and the 4 experimental sessions (with the option of doing an additional 4 experimental trials) will take place at the University of Sydney, Susan Wakil Health Building, Camperdown Campus. The time involvement will be approximately 1 hour for the first preliminary session, and 4 hours for each of the experimental sessions. This involves a total time commitment of approximately 16 hours (or approximately 33 hours if the participant chooses to do an additional four trials). We are recruiting participants for at least four experimental sessions that will take place in the hot, humid condition and providing them with the option of doing an additional four experimental sessions that will be carried out under a different simulated heatwave condition (very hot, dry). These two simulated heatwaves provide very different interactions between the individual, the environment and the proposed interventions and so it is of great importance to study both types. For example, in a previous study carried out in our lab a fan was beneficial in hot-humid conditions due to the increased airflow increasing sweating efficiency and therefore evaporative heat loss, whereas in the hot-dry condition the increased airflow accelerated dry heat gain and so fan-use was actually unfavourable. We understand that the one preliminary sessions and 8 experimental sessions are a big time commitment and so we have chosen to take the above approach to minimize attrition for the primary objective. Investigating the low cost at-home cooling interventions in the hot, humid condition is our primary objective as these are the types of heatwaves most common worldwide. Investigating the same interventions in the very hot, dry condition allows us to investigate their impact in the type of heatwave most prevalent in Australia.

*Pre-screening and preliminary sessions:* Participants will be initially screened over the phone using a standardized phone screen based on the inclusion and exclusion criteria of our study. If the participants pass the phone screen they will be invited in for a preliminary session. The first preliminary session involves a complete medical history, physical examination and cardiac stress test. This screening will be carried out by geriatrician [name]. The following equipment and techniques will be used:

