## 6- Statistics

### 6.1 Sample size

The sample size computation is based on comparison of the primary endpoint (change in rate pressure product from baseline to the end of a 3 hour simulated heatwave exposure to 38°C and

60% RH) between the 4 conditions of control, fan use alone, skin wetting alone, fan use + skin wetting.

The mean and standard deviation of the change in rate pressure product were taken from the preliminary data presented in Figure 3 and are expected to range between 1000 bpm x mmHg and 1700 bpm x mmHg for the mean and between 1700 bpm x mmHg and 2000 bpm x mmHg for the standard deviation. The standard deviation of the difference between conditions is expected to be similar.

The main interest is to compare the control condition with the 3 other conditions taken individually, which implies a significance level of 0.0167 ( $0.05 / 3$ ). A difference of 1250 bpm x mmHg in change in rate pressure product between the control condition and any other condition is judged to be clinically relevant.

In this context a sample size of 30 participants will give 80% power to detect a difference of 1250 bpm x mmHg in change between the control condition and any other condition, assuming that the standard deviation of the difference between conditions is 2000 bpm x mmHg and using a paired t-test with a 0.0167 two-sided significant level. To account for an approximately 10% loss to follow-up rate, 34 participants will be included in the study. Of the 34 participants, 17 will be taking beta-blockers whereas the other 17 will not be taking beta-blockers.

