## 2 STUDY DESCRIPTION

### 2.1 Study Design

The study took place at two sites (Montreal and Sydney). Study participants were asked to volunteer for 1 preliminary visit, 1 screening visit and 4 to 8 study visits. During the study visits, participants were to enter an environmental chamber maintained at either 38°C and 60% relative humidity (RH) (typical North American heatwave condition) or 45°C and 15% RH (typical Australian heatwave condition). For each study visit, the participants were to remain within the environmental chamber and rest in a seated position for 3 hours under various conditions (cooling strategies). In Montreal, the 6 study visits were the following:

- 1) 38°C and 60% RH, no intervention (control)
- 2) 38°C and 60% RH, with fan use
- 3) 38°C and 60% RH, with skin wetting
- 4) 38°C and 60% RH, with fan use and skin wetting
- 5) 45°C and 15% RH, no intervention (control)
- 6) 45°C and 15% RH, with skin wetting.

In Sydney, participants were recruited for 2 preliminary visits and the 4 experimental visits under the North American heatwave exposure with the various cooling strategies. They were also provided with the option of doing additional visits that would be carried under the Australian heatwave exposure with the 4 cooling strategies, resulting in 2 additional visits compared to Montreal:

- 7) 45°C and 15% RH, with fan use
- 8) 45°C and 15% RH, with fan use and skin wetting.

In Montreal, participants were to first undergo the 4 study visits for the simulated North American heatwave exposure to minimize attrition for the primary objective. Participants were subsequently to undergo the study visits for the simulated Australian heatwave exposure. Within each heatwave exposure (North American, Australian) the sequence under which participants would undergo the study visits was randomized. In Sydney, participants were to undergo the 8 study visits in a randomized sequence. Prior to each visit, participants were asked to refrain from strenuous physical activity, alcohol, and caffeine for 12 h. To ensure there is no carry-over effect, study visits were to be performed on separate days, with at least 72 h between visits. Participants prescribed calcium channel blockers were asked to withhold this medication for 48 hours prior to each study visit.

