### 5.2.5 Other exploratory Analysis

To take into account a potential acclimation effect that could occur during the summer, the change in rate pressure product will be analyzed using a REML-based linear mixed model, accounting for repeated measures, including a term for condition, a term for the season (Summer/Not Summer) and the condition x season interaction. This interaction will be tested at the 0.10 significance level and will determine whether the condition effect is impacted by the season. Condition effects will also be estimated and presented with 95% confidence interval within the season category.

The category “Summer” will be assigned to visits that occurred in June, July, August or September at the Montreal site and to visits that occurred in November, December, January, February, March or April at the Sydney site. Otherwise, the “Not Summer” category will be assigned. As season may vary across study visits of a same subject, it will be considered a within-subject factor in the analysis model.

This analysis will be conducted separately under each of the heatwave exposures and will be considered exploratory.

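### No SAP model includes visit order, in a crossover of 4 to 8 heat exposures with different order schemes by site; the cost is mainly precision

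*Supplement*

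**What the plan says.** SAP 5.2.1 compares the four conditions at 38°C and 60% RH with a "linear mixed model including a term for condition and accounting for repeated measures, will be used". On the three contrasts with control it says: "These three comparisons will be tested at the 0.0167 significance level to control for the multiplicity of tests". The hot-dry model in 5.2.2 has the same structure. The models in 5.2.3 to 5.2.5 add beta-blocker use, sex, site or season. None has a term for visit order, period or sequence. The repeated-measures ANOVAs in the two latest protocols have none either; the time factor in the Montreal protocol (6.2) is time within an exposure.

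SAP 2.1 describes two order schemes. In Montreal the four humid visits come first and the two dry visits follow, randomised within each block. For the other site: "In Sydney, participants were to undergo the 8 study visits in a randomized sequence". The Sydney dry visits were optional: the Sydney protocol (4.6) speaks of "providing them with the option of doing an additional four experimental sessions". No design balanced by period is described. Carry-over is handled by a gap of at least 72 h.

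The only model that touches acclimation is exploratory (5.2.5), and its stated aim is seasonal: "To take into account a potential acclimation effect that could occur during the summer".

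**The concern.** Visit order is a design variable in any crossover. Each visit here is a three-hour heat exposure, so a trend across visits from repeated exposure or familiarisation is plausible. A gap between visits is aimed at carry-over from one visit to the next and does not remove a trend over the whole series. Season cannot stand in for order either, because a first and an eighth visit can fall in the same summer.

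If there is a trend, a model with condition alone leaves it in the residual, and every confidence interval is wider than it need be. The site schemes add a second issue. A Sydney humid visit can be anywhere from number 1 to 8, and a Montreal one only 1 to 4. In the hot-dry analysis, Montreal contributes control and skin wetting at positions 5 and 6 only, while both fan conditions come from Sydney alone. There, order is tied to site, and site to condition.

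**Working it through.** **1. The plan's own figure.** Montreal protocol 6.1 states that "a sample size of 30 participants will give 80% power to detect a difference of 1250 bpm x mmHg". Its other inputs are an SD of 2000 for the paired difference and a two-sided paired t-test at 0.0167. The noncentrality is (1250/2000) × √30 = 3.42, which gives 80.5% power. The figure reproduces.

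**2. Inputs.**
- SD of a within-person difference: 2000, so the variance is 4.0 million and the within-person variance per visit is 2.0 million (equal variances assumed).
- Participants: 30 (Montreal) + 45 (Sydney) = 75, the numbers that the two protocols require before allowance for dropout.
- Drift: not in the documents. Assumed linear at 0, 200 or 300 bpm x mmHg per visit. For scale, the expected mean change in Montreal protocol 6.1 is 1000 to 1700.
- Sydney positions: 8 if everyone takes the optional visits (worst case), 4 if nobody does. Uptake is not given.

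**3. Effect of order on a contrast.** For two distinct random positions out of P, the variance of the position difference is [(P²−1)/12] × 2P/(P−1). This is 3.33 for P = 4 and 12 for P = 8. A drift s adds that factor times s² to the variance of a within-person difference.

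With s = 200 and 8 Sydney positions:
- Sydney: 4.0 + 12 × 0.04 = 4.48 million
- Montreal: 4.0 + 3.33 × 0.04 = 4.13 million
- SE = √[(45 × 4.48 + 30 × 4.13) million / 75²] = 241, against √(4.0 million / 75) = 231 with no drift.

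**4. With and without the term.** The columns with the term come from simulation at n = 75 with complete data.

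| Sydney positions | Drift | SE, condition only | SE, order shared across sites | SE, order within site |
|---|---|---|---|---|
| 8 | 0 | 231 | 235 | 236 |
| 8 | 200 | 241 | 234 | 236 |
| 8 | 300 | 252 | 235 | 236 |
| 4 | 0 | 231 | 232 | 234 |
| 4 | 200 | 235 | 232 | 234 |
| 4 | 300 | 239 | 232 | 234 |

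The condition-only model has 222 residual degrees of freedom. A shared order factor uses at most 7 of them. Positions within site use at most 10 (7 in Sydney, 3 in Montreal).

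**5. Bias and type I error.** Simulations at n = 30, with drifts of 0, 300 and 500 and with 4 or 8 positions, gave average estimates close to the true value with and without the order term. Rejection rates under the null were 0.012 to 0.020 against a nominal 0.0167.

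**6. Hot-dry model (5.2.2).** With all 8 visits taken, the mean Sydney position is 4.5; the Montreal mean is 5.5. Under a random-intercept model the two fan contrasts shift, in absolute size, by

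drift × (5.5 − 4.5) × n_M/(n_M + n_S) × v_w/(v_w + 2v_b).

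Here v_w = 2.0 million. The stated SD range of 1700 to 2000 for the change gives total variances of 2.89 to 4.0 million, so v_b is about 0.9 to 2.0 million. With drift 200 and 30 Montreal participants:
- 45 from Sydney, v_b = 2.0 million: 200 × 30/75 × 2.0/6.0 = 27
- 20 from Sydney, v_b = 0.9 million: 200 × 30/50 × 2.0/3.8 = 63

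The skin-wetting contrast is unaffected. Positions defined within site carry a site effect with them, and the shift then becomes zero.

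**The case against.** The strongest reply is that randomisation already protects validity, so what remains is a choice about efficiency. For the primary contrasts with complete data that is correct. A reader might infer that the missing term biases the primary result or inflates its type I error; neither the design nor the simulations support this.

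A reader might also count wider intervals and chance imbalance of order as two harms. They are the same variance: order noise goes into the residual, and the interval already allows for the imbalance. Nor can bias from missed visits be assumed. The Full Analysis set (SAP 3.1) admits incomplete sequences, but if dropout does not depend on condition, the order of control and comparator stays exchangeable among those who have both. The documents show no condition-dependent dropout.

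It is also tempting to say that the SAP itself expects acclimation across visits. Section 5.2.5 speaks of summer. The step to in-trial exposures is an inference, if a short one. The endpoint is a change from each visit's own baseline, so a drift in resting values alone would largely cancel, and the direction of any drift in the change is unknown. The SD of 2000 may already contain order variation.

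Finally, pooled power is hardly at risk. At n = 75 and 8 Sydney positions, power for 1250 is 99.8% with no drift, 99.7% at drift 200 and 99.3% at 300. All of this stands, and it limits the point to precision and robustness. It does not show that order is handled anywhere in the plan, and it does not cover the hot-dry fan contrasts, where condition is tied to site.

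**Conclusion.** The omission is real and runs through every SAP model. Its consequence for the primary analysis is modest. In the worst case for Sydney uptake, an assumed drift of 200 to 300 per visit widens the standard error by about 4 to 9% (241 and 252 against 231), and an order term recovers most of that. If all participants have four positions, the widening is about 2 to 4%; positions within site then roughly break even at drift 200. In the hot-dry model, a drift of 200 would move the two fan contrasts systematically by about 27 to 63 bpm x mmHg, at most 5% of the 1250 judged clinically relevant.

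These sizes rest on an assumed linear drift, complete data, an SD of difference of 2000 free of order effects, and 75 participants. With no drift there is no loss at all. This is a cheap improvement that is better fixed in advance than chosen after the data are seen. It is not a flaw that invalidates the primary contrasts.

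**What to change.** Add visit order as a categorical fixed effect to the models in SAP 5.2.1 and 5.2.2, counting heat exposures in the trial, with positions defined within site because the two order schemes differ. Carry it into 5.2.3 to 5.2.5 where it can be estimated. The beta-blocker models cover participants with CAD, in effect Montreal alone, so only positions 1-4 (humid) and 5-6 (dry) arise there. State what happens if a position is too sparse, for example merging late Sydney positions if few took the optional visits. If the sponsor prefers to keep the primary model as it is, pre-specify the order-adjusted model as a sensitivity analysis.

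No new data should be needed: visit months are already required to assign season, and order follows from visit dates. The price is at most 10 of 222 residual degrees of freedom in the primary model, and a standard error about 1-2% wider if there is no order effect.

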### 5.3 Research protocol

#### 5.3.1 Description of the visits

Upon awakening the day of a study visit, participants will be asked to swallow an ingestible telemetric pill which will have been provided to them beforehand. Upon arrival to the laboratory, participants will be asked to provide a urine sample, self-insert a rectal temperature probe and weigh themselves nude (in private). Participants will then be instrumented following which they will rest in the seated position for a 10 min baseline period at a room temperature of 24°C. Following this baseline period, they will enter an environmental chamber maintained at either 38°C and 60% RH or 46°C and 10% RH and will be seated on a mesh chair that will allow for convective airflow. Participants will remain seated for 3 hours within the environmental chamber while the relevant cooling intervention is administered. During the exposure, heart rate will be measured continuously from an ECG signal and blood pressure measurements will be taken every 20 minutes by automated auscultation of the brachial artery. Rate pressure product (**RPP**) will subsequently be calculated at baseline and every 10 minutes during the 3 hour exposure (see arrows in timeline below). Participants will be provided with 3 ml/kg of water every hour. At the end of the 3 hour period, participants will exit the environmental chamber to be de-instrumented and will be asked to weigh themselves nude in private to calculate whole-body sweat rate. During the study visits with fan use, an 18" diameter fan will face the participant from a distance of 1.0 m to provide an airflow of 4.0 m/s. During the study visits with skin wetting, tap water (~18°C) will be sprayed to the forehead, face, arms, lower legs and neck with a bottle every 5 minutes.

[figure not shown]

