### 5.2.2 Secondary Analysis

Descriptive statistics (mean, standard deviation, median, Q1, Q3, minimum and maximum) will be presented for the change in rate pressure product from baseline to end of a 3-hour simulated heatwave exposure at 45°C and 15% RH. The change in rate pressure product will be analyzed using a REML-based linear mixed model including a term for condition and accounting for repeated measures. Contrasts under this model will allow for the three following comparisons:

- Control vs. fan alone
- Control vs. skin wetting alone
- Control vs. fan + skin wetting

The difference between the control condition and each of the 3 other conditions will be presented with point estimate along with 95% confidence intervals.

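### The RPP models analyse raw change without the visit's own baseline as a covariate, forgoing a nearly free gain in precision of uncertain size that may be close to zero

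*Supplement*

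**What the plan says.** SAP 4.1 defines the endpoint as the change in RPP from pre-exposure to the end of the 3-hour exposure. SAP 5.2.1 fits a REML-based "linear mixed model including a term for condition and accounting for repeated measures", which "will be used to compare the change from baseline in rate pressure product under the 38°C and 60% RH heatwave exposure". It tests three contrasts against control at 0.0167, with 98.33% intervals. SAP 5.2.2 uses the same form at 45°C, "including a term for condition and accounting for repeated measures". SAP 5.2.3 to 5.2.5 add beta-blocker, sex, site or season and their interactions with condition. None of these models names baseline RPP.

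A baseline exists at every visit. In the amended Montreal protocol (5.3.1), after instrumentation "they will rest in the seated position for a 10 min baseline period at a room temperature of 24°C", and RPP "will subsequently be calculated at baseline and every 10 minutes during the 3 hour exposure". The amended Sydney protocol (4.6) has 30 minutes of seated rest at about 24°C, during which participants are instrumented, before they enter the chamber.

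The Montreal sample size (6.1) was computed for the raw change: "a sample size of 30 participants will give 80% power to detect a difference of 1250 bpm x mmHg in change", with an SD of the difference of 2000, "using a paired t-test with a 0.0167 two-sided significant level".

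**The concern.** Each visit's baseline is taken before the chamber and before the cooling condition, so it is a legitimate covariate. In a crossover, stable differences between participants already drop out of the condition contrasts. What remains is visit-to-visit variation within a participant. A single-visit RPP (heart rate times cuff systolic pressure) carries measurement noise and day-to-day variation. Subtracting it in full carries that noise into the endpoint unless the within-participant slope of end value on baseline happens to be 1. Estimating the slope lets the data decide how much to subtract.

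At stake is the width of the intervals for every RPP contrast. Width matters because the objective is to find the best strategy, not only to reject zero, and because the same model is carried into much smaller comparisons than the primary one.

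**Working it through.** **The plan's own figure.** Exact paired t-test, difference 1250, SD 2000, two-sided 0.0167, n = 30: noncentrality 1250/2000 × √30 = 3.42 on 29 df, power 80.5%. With n = 29 it is 78.8%. Then 30/(1 − 0.10) = 33.3, so 34. The Montreal calculation reproduces.

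**Formula.** Let s be the within-participant visit-to-visit SD of baseline, ks that of the end value, and r their correlation within a participant.

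- Raw change: contrast variance proportional to s²(1 + k² − 2rk).
- Slope estimated: proportional to s²k²(1 − r²).
- Share saved: 1 − k²(1 − r²)/(1 + k² − 2rk) = (1 − rk)²/(1 + k² − 2rk).

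The saving is zero when rk = 1, for example r = 0.5 with k = 2. With k = 1 it reduces to (1 − r)/2.

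**Inputs.** The Montreal protocol (6.1) gives only the mean and SD of the change. The values of r and k below are assumptions.

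| k | r = 0.3 | r = 0.5 | r = 0.7 |
|---|---|---|---|
| 0.8 | 50% | 43% | 37% |
| 1 | 35% | 25% | 15% |
| 1.25 | 22% | 11% | 2% |
| 1.5 | 13% | 4% | 0.2% |

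A simulation with 30 participants and 4 conditions gave savings of 34%, 27% and 13% along the k = 1 row. At k = 1.5 with r from 0.5 to 0.7 it gave between −2% and +3%, because estimating the slope uses up a very small gain.

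**What savings of 15%, 25% or 35% would mean.** Interval width is multiplied by √(1 − saving) = 0.92, 0.87 or 0.81.

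- Montreal alone, n = 30: power rises from 80.5% to 87%, 91% or 95%.
- Pooled, n = 30 + 45 = 75 (both protocols' numbers before inflation for loss), assuming SD 2000 also holds in Sydney: power for 1250 is already 99.8%. The difference detectable with 80% power falls from 762 to 702, 660 or 614.
- One beta-blocker stratum, 17 planned, alpha 0.05, SD 2000: noncentrality 1250/2000 × √17 = 2.58 on 16 df. Power rises from 68% to 75%, 80% or 85%, and the 95% half-width falls from 1028 to 948, 891 or 829. These figures use all 17, before any loss.

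The 45°C fan contrasts cannot be sized in the same way. They rest only on Sydney participants who take up the optional visits (SAP 2.1), and the documents do not give that number.

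**The case against.** The strongest reply is that nothing is wrong. Endpoint, protocol model and sample size all use the raw change, so the analysis delivers the power that was planned. All of this stands.

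The gain may also be small. An SD of the difference of 2000 implies a within-participant SD of change of about 2000/√2 = 1414, if visits are independent given the participant. For k = 1 the resting baseline would then have to vary between visits with SD 1414/√(2(1 − r)) = 1195, 1414 or 1826 at r = 0.3, 0.5 or 0.7. That is about as large as the expected mean rise of 1000 to 1700. If the resting SD were instead 1000 (an assumption), the same formula gives savings of 18%, 2% and 6%. The documents cannot settle which case applies, so this also stands.

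A reader might infer that chance baseline imbalance biases the contrasts through regression to the mean. The documents do not support that. Visit order is randomised, so the raw-change contrast is unbiased. Chance imbalance is the same variance seen from another side, not a second harm.

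Finally, the baseline procedures differ: 10 minutes after instrumentation in Montreal, and 30 minutes that include instrumentation in Sydney. Baseline noise, and hence the slope, may differ by site. That is a reason to specify the covariate with care, not to leave it out.

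**Conclusion.** The RPP models leave out a covariate that is already collected at every visit and that would probably tighten the intervals. In large samples adjustment cannot increase the contrast variance. In samples of this size the worst case simulated was a loss of about 2%. Over the grid shown the saving runs from about 0% to 50%, depending on r and k, and neither is in the documents.

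Two stronger readings are tempting and should be resisted. One is that the plan gives away 15 to 35% of the variance of every primary contrast. That needs k = 1 together with r between 0.3 and 0.7. The other is that primary power is at risk. Montreal alone meets its stated 80%, and pooled power for 1250 is about 99.8% if SD 2000 applies at both sites.

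The practical value lies in interval width, above all within the beta-blocker strata and for the 45°C fan contrasts. It is an efficiency improvement that is worth making because it costs almost nothing.

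**What to change.** In SAP 5.2.1 to 5.2.5, add visit-specific baseline RPP to each RPP model as two covariates: the participant's mean baseline over the visits analysed, and the visit's deviation from that mean. The split keeps the within-participant slope, which bears on the condition contrasts, separate from the between-participant slope. The contrasts still estimate the difference in change. Do the same for core temperature, thermal comfort and thermal sensation in 5.2.3. Let the within-participant slope differ by site if the two baseline procedures are thought to warrant it. Keep the unadjusted change model as a sensitivity analysis, and state before the data are analysed which of the two is primary, so that the choice cannot depend on the results.

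The cost is a short SAP amendment and about two degrees of freedom per model, slightly more with site-specific slopes. No new data are needed.
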